### Sample size

The sample size is calculated based on data on adult female *Aedes* mosquitoes collected using mechanical aspirators (15 min outdoors and indoors each) from a case-control study in nearby districts during 2016 and 2017. The mean capture was 0.78 mosquito per house (indoors + outdoors). At minimum, 34 clusters are needed to detect a 90% difference in adult female mosquitoes per house with 90% statistical power and a two-sided significance level (α) of 0.05 assuming 10 households are visited three times each after the intervention begins and a between-cluster coefficient of variation of 0.33. Sample size methods for cluster-randomized trials were used [49], as implemented in the ‘clustersampsi’ add-on to Stata® statistical software [50]. The existing data were over-dispersed relative to a Poisson distribution; therefore, to represent a negative binomial distribution with a dispersion parameter (α, or 1/*k*) of 2.03 estimated from the same data, the ‘means’ option was used, with the variance in each arm equal to the mean plus the square of the mean times α [51]. The clusters are split equally between the strata (Khon Kaen and Roi Et). To provide an equal number of clusters in each arm, one extra cluster is added per stratum, i.e., 18 clusters per stratum (city) and 9 clusters per arm in each stratum.

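### The printed sample size inputs do not give 34 clusters for a 90% difference, so the effect size or at least one input is misprinted and must be reconciled

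*Protocol article*

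**What the plan says.** Everything is in one paragraph of the protocol article, under Sample size. The starting value comes from a case-control study in nearby districts: "The mean capture was 0.78 mosquito per house (indoors + outdoors"). The requirement is that at minimum "34 clusters are needed to detect a 90% difference in adult female mosquitoes per house with 90% statistical power". The test is two-sided at the 5% level. On cluster size and clustering, the calculation is described as "assuming 10 households are visited three times each after the intervention begins and a between-cluster coefficient of variation of 0.33". The software is a Stata add-on for cluster-randomized trials, run with its option for means. Over-dispersion is handled by a negative binomial dispersion of 2.03, "with the variance in each arm equal to the mean plus the square of the mean times α". The 34 clusters are then raised to 36, that is 18 per city and 9 per arm in each city, so that the arms are equal within strata.

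**The concern.** This sentence is the only justification given for the size of the trial, and it concerns the primary outcome, the Adult index. Because the section prints the mean, variance rule, cluster size, CV, power and significance level, the required number can be recomputed without any assumption from outside. A 90% fall in a count is a very large effect and a between-cluster CV of 0.33 is moderate, so 17 clusters of 30 house visits per arm looks like far too many.

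If the sentence is wrong, a reader cannot tell which trial was designed. With a CV of 0.33, the design detects a reduction of well under half. If 0.33 was really an ICC, the same 36 clusters are just sufficient for near-elimination and would usually miss a halving. These are very different statements about what the trial can show.

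**Working it through.** **Inputs (all from the Sample size section).** Control mean μ₁ = 0.78. Variance v = μ + 2.03μ². Observations per cluster m = 10 × 3 = 30. CV = 0.33. Power 90%, two-sided 0.05, so (1.960 + 1.2816)² = 10.507. Stated result: 34 clusters, 17 per arm.

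**Formula.** For two means with a between-cluster CV, clusters per arm are

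c = 1 + 10.507 × [(v₁ + v₂)/m + CV²(μ₁² + μ₂²)] / (μ₁ − μ₂)²

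**Step 1: try to reproduce 34 from a 90% reduction (0.78 to 0.078).**
- v₁ = 0.78 + 2.03 × 0.6084 = 2.0151; v₂ = 0.0904
- (v₁ + v₂)/30 = 0.0702
- CV²(μ₁² + μ₂²) = 0.1089 × (0.6084 + 0.0061) = 0.0669
- (μ₁ − μ₂)² = 0.702² = 0.4928
- c = 1 + 10.507 × 0.1371/0.4928 = 3.92, so 4 per arm, 8 clusters

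Without the +1 the result is 2.92 (3 per arm, 6 clusters). With t-quantiles it is 5 per arm (10 clusters). The stated 34 is not reproduced. At 17 per arm the power for a 90% reduction exceeds 99.9%. Counting the three visits to a house as one (m = 10) gives only 6.92, so 7 per arm.

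**Step 2: other readings of a 90% difference, with m = 30 and the +1.**

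| Reading | Means | c | Total clusters |
|---|---|---|---|
| 90% reduction | 0.78 to 0.078 | 3.92 | 8 |
| 90% increase | 0.78 to 1.482 | 13.17 | 28 |
| Control 1.9 × intervention | 0.78 and 0.4105 | 14.61 | 30 |

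None gives 34.

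**Step 3: what effect do 34 clusters match on the printed inputs?** For a 45% reduction (0.78 to 0.429):
- v₂ = 0.8026; (v₁ + v₂)/30 = 0.0939
- 0.1089 × (0.6084 + 0.1840) = 0.0863
- (μ₁ − μ₂)² = 0.1232
- c = 1 + 10.507 × 0.1802/0.1232 = 16.37, so 17 per arm, 34 clusters

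Solving exactly for 17 per arm gives 44.2% with the +1 and 43.1% without. For the planned 18 per arm the figures are 43.1% and 42.1%.

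**Step 4: can one changed input restore 34 while keeping a 90% reduction?** Yes, in at least two ways.
- *0.33 as an ICC.* Individual sample size per arm is 10.507 × (2.0151 + 0.0904)/0.4928 = 44.9. The design effect is 1 + 29 × 0.33 = 10.57. Clusters per arm are 44.9 × 10.57/30 = 15.8, which is 16 per arm, or 17 with the +1 (16.8) or with t-quantiles.
- *Three observations per cluster instead of 30.* Without the +1: 10.507 × (2.1054/3 + 0.0669)/0.4928 = 16.4, so 17 per arm.

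**Step 5: why the choice matters.** If 0.33 is an ICC, the standard error for a 45% reduction at 18 per arm is √[(2.0151 + 0.8026) × 10.57/(30 × 18)] = 0.2348. Then 0.351/0.2348 − 1.960 = −0.465, which is a power of about 32%. At 17 per arm it is about 31%. On the CV reading, the power for the same effect at 17 per arm is 91–93%.

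**The case against.** The strongest reply is that the document says difference, not reduction. Read as control 90% above intervention, the same inputs give 30 clusters, a shortfall of 4 and not 26. The primary analysis does report a between-arm ratio, so this reading is possible. It still does not give the stated number, and the hypothesis at the end of the Background is a lower density in the intervention arm, which makes a 90% reduction the natural reading.

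A second reply stands in full. Because a 45% reduction returns exactly 34, a reader might infer that 90% is simply a slip for 45% and can be overwritten. The document does not support that. The ICC route reaches 34 with the 90% kept, and under it a claim of 90% power for a 45% reduction would be wrong by a factor of about three.

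A reader might also infer that, as written, a null result would exclude only a 90% effect. It would not: what a null result excludes depends on the confidence interval of the estimated ratio, not on the planning effect.

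Finally, treating three visits to one house as independent is optimistic. Its cost cannot be computed from the document, since no within-house correlation is given. Extra monthly sentinel collections and adjustment for baseline may work the other way. It belongs in the text as a stated assumption, not as a further error.

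**Conclusion.** The sentence is wrong as printed. On its own inputs, a 90% reduction needs about 8 clusters (6 to 10 across formula variants that keep those inputs), roughly a quarter of the stated 34. No other reading of the 90% reaches 34. If the CV of 0.33 and the 30 observations are right, 34 clusters match a reduction of about 44–45% and 36 match about 42–43%. These figures rest on the standard two-means formula with the per-arm variances given and with repeat visits counted as independent.

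Confidence is high that the printed figures are mutually inconsistent. The document does not settle whether the error lies in the effect size, in the label of the 0.33 or in the observations per cluster. Nor does it show that 36 clusters are too few or too many.

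**What to change.** Retrieve the original program output and reconcile three items against it: the effect size, whether 0.33 was entered as a CV or as an ICC, and the number of observations per cluster. Then restate the sentence so that a reader can reproduce it.

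- If CV 0.33 and 30 observations are confirmed, state a detectable reduction of about 44–45% with 34 clusters (about 43% with the planned 36), and add that repeat visits to a house are treated as independent.
- If 0.33 was an ICC, keep the 90% reduction, correct the label, and make no claim of 90% power for a 45% reduction, for which the power would be about 30%.
- If 3 observations per cluster were entered, say so and rerun with the number that the design provides.

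The cost is a look at the stored output and one or two sentences of text. The number of clusters does not change.

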### Eligibility criteria

Eligibility for participation in the trial is determined on four levels: (1) location or village, (2) cluster of houses within village, (3) households within cluster, and (4) individuals within households (household residents) (Table 2).

**Table 2 Tab2:** Eligibility criteria by location, cluster, household, and individual

Level	Inclusion criteria	Exclusion criteria
Village	- Within ring roads of each city (stratum)	- Area < 0.125 km^2^
	- Populated residential areas	- Number of houses < 100
		- Population < 300
		- Coverage of residential area 70–80% (scattered housing)
		- Non-residential areas, e.g., agricultural fields, airports, industrial areas, commercial areas, (e.g., shopping malls), government offices, lakes, army camps, hospitals, and schools
Cluster	- All points of the cluster are at least 100 m from the nearest point of the village border	
Household	- Households that are permanently inhabited	- Apartment buildings
		- Abandoned houses
	- Households that are built or re-populated during the study period	- Non-permanent households
Individual	- Individuals in households where household head has signed informed consent for household to participate in project	- A travel history outside the village during the previous 7 days
	- Self-reported fever within the last 7 days	- Chronic disease, such as HIV/AIDS, or other health condition that preclude participation in the study
	- Age ≥ 1 year old	- Apparent inability to give informed consent, e.g., due to mental disability

There is a distinction between being included in the final evaluation of endpoints and inclusion for receiving interventions. For example, abandoned houses and non-permanent household structures are not included in evaluation of endpoints, but they may be treated with an intervention if they are located within a radius of 100 m and as feasibly possible

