### Recruitment

The 162 villages in Khon Kaen and 39 villages in Roi Et located within the respective ring roads are the sampling frames for each stratum. In each stratum, villages are randomly sampled based on probability proportional to population size, i.e., the population of occupied houses (the target denominator of the primary endpoint). These selected villages will be randomly allocated between the arms (see the section on Assignment of interventions below).

Villages are normally much larger than the target cluster size (10 houses); therefore, to select a starting point for the house selection, a 50 × 50 m grid and a 100-m buffer zone inside of the village perimeter will be superimposed over each village map. The buffer zone of approximately 100 m on the inside of each village border is applied to reduce potential “contamination” (in-flying mosquitoes) from neighboring villages. A random grid cell is selected in each village and 10 houses nearest the centroid of that cell selected. This procedure is followed in each village in this manner as far as practically possible. For example, if a selected household does not want to participate in the study, a neighboring house will be selected.

Informational meetings are held at the sub-district and village administrative levels to provide information about the project and benefits to the communities. Householders are visited and carefully informed about the study, and informed consent is obtained from the household head. A complete enumeration of all participants in the selected clusters will be completed with assistance from the local administration and village health volunteers (VHVs). This enumeration will be done three times during the study, allowing monitoring of potential participants’ discontinuation in the trial. Data on discontinuation, whether due to movement outside the study area or withdrawal of consent, are relevant for the secondary outcomes of DIR and MEI. Reasons for potential discontinuation will be monitored and taken into account in communication strategies to promote retention. In addition, a minor monetary compensation for those who provide blood samples for the mosquito exposure study will promote participant retention to complete follow-up of individuals.

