### Interventions

Following approximately 10–12 months of baseline data collections, household interventions will begin in the selected intervention clusters (Fig. 2). The intervention specifically targets mosquito immature stages by applying a mixture of pyriproxyfen and spinosad to all permanent household containers, whether indoor or outdoor, found to contain water up to a 10-m perimeter from the house. Pyriproxyfen is an insect growth regulator (insect juvenile hormone analog) that is active against pupal stages, resulting in the inhibition of adult development (preventing emergence). It has low mammal toxicity and is recommended by WHO for vector control [52]. Spinosad is a natural insecticide produced by the soil bacterium *Saccharopolyspora spinosa*. It has a neurotoxic mode of action in insects, but with low mammal toxicity, and it is also recommended by WHO [52]. The doses recommended by WHO for *Aedes* immature mosquito control are 0.01 mg/L active ingredient (a.i.) pyriproxyfen (applied as a 0.5% granule formulation) and 0.1–0.5 mg/L a.i. spinosad (also a 0.5% granule formulation) [45, 53]. Both pyriproxyfen and spinosad have also been assessed and approved by WHO for use in drinking water containers [54, 55]. The reasons for selecting this novel intervention are that the combination of pyriproxyfen and spinosad has not yet been tested in a national dengue vector control program; that it should be effective, easy, and practical to use for national control authorities; and that its combined use reduces the risk of resistance development. The interventions will be implemented by project staff from the Ministry of Public Health, thereby ensuring adherence to intervention protocols.

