### Assignment of interventions

#### Sequence generation and implementation

The assignment of intervention (allocation) and control to clusters will be accomplished by two open public lottery events, one in each city (Fig. 2). Allocation will be done several months after and independently from cluster recruitment (Fig. 2). The lottery events will be carried out just before the first intervention. Representatives from each respective sub-district and village, including householders, district village heads, VHVs, and sub-district hospitals, will be invited to attend. Information about dengue and the purpose of the project will be provided. The reasons for randomization, its procedures, and the concepts of intervention and control will be explained. Attendants will also have a chance to ask questions about dengue, vector control, health-seeking behaviors, personal experiences of dengue, and specific details about the project.

Each of the two lotteries will be performed as follows. Small pieces of paper, of the same color and size and thus indistinguishable from one another, numbered from 1 to 18, will be folded and placed in small opaque envelopes and then placed in a bowl. Each number represents a cluster (village). A large screen with the numbered list of village names (from 1 to 18) will be shown above the bowl and visible to all. A person not involved in the study, and accepted by all participants, will be selected to make the draw. Two flip boards with large sheets of paper will be placed on either side of the bowl with the respective headings “Intervention” and “Control” (in Thai). The village on the first paper drawn will be assigned to the intervention arm, the village on the next paper drawn will be assigned to the control arm, and so on. Following the draw, the implications of being in either of the two arms will be discussed and the roles of participants, health volunteers, and sub-district hospital staff will be reviewed. By following this lottery scheme, the interventions are allocated at the same time as the sequence is generated, obviating the need for allocation concealment.

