#### Blinding

This study is unblinded for both participants and data collectors because of the nature of the intervention and because it is neither practical nor financially feasible to obtain placebo (blank) granules of pyriproxyfen and spinosad to serve as a control. However, although knowledge of treatment allocation could affect mosquito endpoints (e.g., differential collection efforts), the MEI, which relies on the antibody response to *Ae. aegypti* saliva, should not be affected significantly. In terms of performance bias (i.e., systematic differences in care), dengue incidence is an endpoint, and dengue may initiate contact with health care personnel. However, the subsequent course of the episode does not affect any of the endpoints. In other words, care from health personnel will not affect the dengue diagnosis status, so performance bias should not be a concern.

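### Table 2 lets newly built or re-populated houses enter the endpoint evaluation after the public lottery, a small recruitment-bias gap in an unblinded trial

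*Protocol article*

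**What the plan says.** The household row of Table 2 (Eligibility criteria) lists as an inclusion criterion "Households that are built or re-populated during the study period". The note under the table separates being evaluated from being treated, and the structures it names as outside evaluation are these: "abandoned houses and non-permanent household structures are not included in evaluation of endpoints". New and re-populated houses are not among them.

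The Recruitment section fixes the initial sample: "A random grid cell is selected in each village and 10 houses nearest the centroid of that cell selected". As an example of how this works in practice, it adds that "if a selected household does not want to participate in the study, a neighboring house will be selected".

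On timing, Sequence generation and implementation says "Allocation will be done several months after and independently from cluster recruitment", and places the two public lotteries just before the first intervention. The Interventions section dates that start: "Following approximately 10–12 months of baseline data collections". The Blinding section says "This study is unblinded for both participants and data collectors" and accepts that knowing the allocation could affect mosquito endpoints.

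Entomological collections cover every participating household. The primary model takes each cluster's total of female adults over its total of house visits, with the cluster's pre-intervention value as a covariate. Neither Analysis populations nor Statistical methods treats houses that enter after the lottery differently from the others.

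**The concern.** In an unblinded cluster trial, the usual guard against recruitment bias is to enrol the units to be measured before anyone knows the arm. The plan does this for villages and for the initial ten houses in each. The Table 2 criterion runs through the whole study period, so it also admits houses whose occupants are approached when the arm is already public. Willingness to join could then differ between villages that receive the larvicide and villages that receive nothing from the project. Any resulting difference in the type of house enters the Adult index contrast.

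The baseline covariate would not pick this up for a newly added house, because that house contributed nothing to the cluster's pre-intervention value.

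**Working it through.** The plan gives no figure for late entry, so there is none to reproduce. The check has two parts.

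**1. Can a house enter after the arm is known and still be counted?**

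- Eligibility runs over the study period (Table 2), which is 2 years of data collection (Abstract).
- The lottery falls at about month 10–12 (Interventions; Sequence generation and implementation). The window after it is 24 − 12 = 12 to 24 − 10 = 14 months, or 50% to 58% of the study.
- The evaluation exclusions in the note to Table 2 do not name such houses, collections cover all participating households, and the primary model sums over all house visits in the cluster.

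On the plain text, the answer is yes.

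**2. How much could it matter?**

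Inputs from the plan: 10 houses per cluster, 3 of them sentinel houses visited monthly, and all houses visited every 4 months (Recruitment; Table 1); 9 clusters per arm in each of two cities, so 18 per arm (Sample size).

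Assumptions: a 12-month intervention period, with the 4-monthly rounds coinciding with monthly visits in sentinel houses.

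- Visits per cluster: 7 × 3 + 3 × 12 = 57.
- Share from one non-sentinel house present for the whole period: 3/57 = 5.3%. A house that joins later supplies less.
- If the 4-monthly rounds were extra visits in sentinel houses: 10 × 3 + 3 × 12 = 66, and 3/66 = 4.5%. If only the 4-monthly rounds counted, as in the sample-size assumption: 3/30 = 10%.
- Share of an arm's visits from one such house: 3/(18 × 57) = 3/1026 = 0.29%.

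Let a share q of one arm's post-lottery visits come from late entrants whose expected Adult index is g times that of the other houses. That arm's index is multiplied by 1 − q + q × g. Neither q nor g is in the plan, so a range is assumed:

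| q | g = 0.5 | g = 2 |
|---|---|---|
| 2% | 0.99 | 1.02 |
| 5% | 0.975 | 1.05 |
| 10% | 0.95 | 1.10 |
| 20% | 0.90 | 1.20 |

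For scale, q = 5% needs roughly one late non-sentinel house, present from the start, in each of the 18 clusters of an arm. The multiplier is approximate at arm level, because the negative binomial model does not weight clusters exactly by their visits. It becomes a bias in the ratio between arms only to the extent that it differs between them.

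**The case against.** The strongest reply is that an open sample is a legitimate choice. The intervention is area-wide, the Trial design section wants clusters to resemble scaled-up use, and newly occupied houses belong to that area. Building or re-occupying a house is not itself an act of enrolment that depends on the arm. The plan describes no procedure for adding houses beyond the ten selected. A re-populated house may be one already in the sample, with its own earlier collections, and the Adult index is counted per house, not per occupant. The baseline term is there to reduce residual error, not to match houses. The bias is small beside the 90% difference for which the trial is sized, and an article may leave detailed handling to a fuller document.

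Most of this stands and limits the size of the point. It does not remove it. Consent from new occupants can depend on a known arm even when construction does not. The criterion is also a stated rule with an open end, not a detail left out. An area-level aim can be served by a sensitivity analysis that includes the newer houses.

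A reader might go further in three ways that the plan does not support:

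- **Refusals replaced by neighbours throughout the trial.** The neighbour rule is an example within the initial house selection, and that step precedes allocation. Trial status reports that household participation had been requested and baseline collections started in Khon Kaen. Nothing says that later withdrawals are replaced, or who chooses the neighbour. The repeat enumeration ("This enumeration will be done three times during the study") is described as monitoring discontinuation, not as a recruitment round.
- **A late sentinel house supplying 12/57 = 21% of a cluster's visits.** Sentinel houses are the same ones each time, and no replacement of them is described.
- **Every late entrant lacking a baseline.** This holds for a newly added structure, but not for an enrolled house with new occupants.

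**Conclusion.** The point holds in a limited form. Table 2 admits houses to the evaluation after the arm is publicly known, and nothing in the analysis sections separates them. This leaves a gap in the protection from recruiting before allocation. It would be wrong to infer that the safeguard is undone, since all villages and the initial houses are recruited before the draw.

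The likely bias is small: a factor of about 0.975 to 1.05 in one arm's Adult index if 5% of its visits come from entrants with half to twice the usual index. It reaches 0.90 to 1.20 only if one visit in five comes from such houses. These figures rest on assumed values of q and g and on the 57-visit schedule. The bias matters only if late entry is both common and selective by arm, and the plan gives no information on either.

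**What to change.** State in Table 2 and in Analysis populations that the primary Adult index and the other entomological comparisons use houses, meaning structures, enrolled before the lottery, with whatever visits they contribute. Keep enrolled houses whose occupants change. Houses first enrolled after the lottery may still be treated and visited, but count only in a sensitivity analysis. Report late entries by arm, for example in the planned flowchart.

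This takes a sentence in each place and should be settled before the lotteries. The price is slightly fewer house visits and a little less coverage of newly built housing in the primary comparison; the sensitivity analysis recovers both.
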